## Abstract

**Background:**

Few prospective longitudinal studies have been conducted in Thailand to account for the long-term response to chronic urticaria (CU) treatment, clinical outcomes, and patient-reported outcomes (PROs) among people living with CU based on routine practice. As such, a prospective longitudinal study will be conducted to better understand the long-term responses to treatment options and the burden of disease in Thai CU patients.

**Methods and design:**

This study is a routine clinical practice registry-based, monocentric, prospective, observational longitudinal study in the northern region of Thailand. Adult patients in an outpatient clinic diagnosed with CU, including both chronic spontaneous urticaria and chronic inducible urticaria will be recruited for this study. The cohort will be collected and registered using the joint routine clinical practice data based on multiple datasets including claims outpatient and inpatient data, routine laboratory results, medication utilization, health care costs, clinical characteristics, long-term urticaria care and monitoring, and PRO measures. The point prevalence of adverse health outcomes will be estimated and reported corresponding to 95% confidence intervals (95% CIs). The overall trend analysis will be analyzed to explore the effect of over time across the cohort time frame.

**Conclusion:**

This prospective longitudinal study will report the clinical outcomes, PROs, and economic burden among Thai people living with CU based on routine clinical practice. Findings will provide comprehensive evidence and could facilitate best practices for CU care management for health care professionals, researchers, policymakers, and public society.

**Trial registration:**

Thai Clinical Trials Registry (TCTR, thaiclinicaltrials.org) registration TCTR20210706005. Registered on July 6, 2021.

## Introduction

Chronic urticaria (CU) is a chronic inflammatory skin disease characterized by the presence of recurrent hives (wheals), and/or angioedema for longer than six weeks [1]. According to global epidemiology estimates, CU is a common disease that affects adults, with a point prevalence of 0.86% [2]. However, it has been revealed to increase over time, in particular, up to 1.5% in Latin America and 1.4% in Asian countries [2]. CU is recognized as chronic spontaneous urticaria (CSU, lesions occur spontaneously), chronic inducible urticaria (CIndU, lesions occur in response to explicit triggers), or both (co-existence of CSU and CIndU). With respect to the subtypes of CU, approximately two-thirds of patients with CU were characterized as CSU [3], and 20.2% of patients were diagnosed as having a combination of CSU and CIndU [4].

On the basis of patient and society’s perspective, individuals living with CU are significantly negatively affected by a wide spectrum of disease burdens, including high impact on health-related quality of life (HRQOL), impaired school/work performance, limited activity and physical function, worsened mental health and well-being issues, psychosocial problems (i.e., impaired family life, partnerships, and social interactions), and high costs and economic burden [5–9]. Moreover, existing studies have revealed that CU patients place a significant burden of illness higher than other chronic skin diseases [9, 10].

Although the current European Academy of Allergology and Clinical Immunology (EAACI)/Global Asthma and Allergy European Network (GA^2^LEN)/European Dermatology Forum (EDF; EuroGuiDerm)/Asia Pacific Association of Allergy, Asthma and Clinical Immunology (APAAACI) international guidelines suggest effective licensed doses of non-sedating second-generation H1-antihistamines as the first-line therapy for the management of CU and there is substantial evidence of its effectiveness [1, 11], CU patients are often inadequately controlled for urticaria symptoms with this first-line therapy [3, 8, 12, 13].

To the best of the researcher’s knowledge, there are very few prospective longitudinal studies in Thailand to account for the long-term response of CU treatment, clinical outcomes, and patient-reported outcomes (PROs) among people living with CU based on routine practice. As such, this study aim to develop the CORE-CU (Clinical Outcomes, Patient-Reported Outcomes, and Economic Burden for Thai People Living with Chronic Urticaria), a monocentric prospective cohort study, to better understand the long-term responses to treatment options and the disease burden in Thai CU patients.

### Objectives

#### Primary objectives

To evaluate and track the treatment response and clinical outcomes among adult CU patients during routine urticaria care management.To assess the impact of CU on long-term PROs, including HRQOL, symptom burden, mental health issues, well-being, and psychosocial problems.

#### Secondary objectives

To establish and validate the clinical utility of the PROs in daily practice.To explore the economic burden of people living with CU, including medication utilization, health care costs, and out-of-pocket costs, in the Thai CU cohort.

## Material and methods

### Study design

The Clinical Outcomes, Patient-Reported Outcomes, and Economic Burden for Thai People Living with Chronic Urticaria (CORE-CU) is a routine clinical practice registry-based, monocentric, prospective, observational longitudinal study at the urticaria clinic, Maharaj Nakorn Chiang Mai Hospital, a northern region of Thailand. This study was registered with the Thai Clinical Trials Registry (thaiclinicaltrials.org; TCTR20210706005, July 6, 2021).

### Study population

Adult patients in an outpatient urticaria clinic will be consecutively recruited for this research. The study population will consist of adult patients diagnosed with CU (duration >6 weeks) based on the EAACI/GA^2^LEN/EuroGuiDerm/APAAACI Guideline on urticaria [1]. Both CSU and CIndU are included (Table 1). The inclusion and exclusion criteria for the longitudinal cohort are shown in Table 2.

**Table 1 pone.0279566.t001:** Classification of chronic urticaria subtypes [1].

**Chronic spontaneous urticaria (CSU)**
• Spontaneous appearance of wheals, angioedema or both due to known (i.e, auto-reactivity—that is the presence of the mast-cell activating auto-antibodies) or unknown causes
**Chronic inducible urticaria (CIndU)**
• Symptomatic dermographism (urticaria factitia or dermographic urticaria)
• Delayed pressure urticaria (pressure urticaria)
• Solar urticaria
• Aquagenic urticaria
• Contact urticaria
• Cold urticaria (cold contact urticaria)
• Heat urticaria (heat contact urticaria)
• Cholinergic urticaria
• Vibratory angioedema

**Table 2 pone.0279566.t002:** Eligibility criteria of the CORE-CU study.

**Inclusion criteria**	**Exclusion criteria**
• Participants aged ≥18 years at the date of screening	• Any conditions (both mental or physical) that would interfere with the participant’s ability to comply with the study protocol
• Diagnosed with chronic urticaria based on the EAACI/GA^2^LEN/EDF/APAAACI guideline: had wheals and/or angioedema for >6 weeks	
	• The prognosis for survival <12 months
	• A primary skin disorder that could explain the pruritus or angioedema (i.e., cholestatic liver disease, atopic dermatitis, bradykinin-mediated angioedema, Bullous pemphigoid, Well’s syndrome, Schnitzler’s syndrome, etc.)
• Had an ability to understand and willingness to sign an informed consent statement	

Abbreviations: APAAACI, Asia Pacific Association of Allergy, Asthma and Clinical Immunology; CORE-CU, Clinical Outcomes, patient-Reported outcomes, and Economic burden for Thai people living with Chronic Urticaria; EAACI, European Academy of Allergology and Clinical Immunology; EDF, European Dermatology Forum (EuroGuiDerm); GA^2^LEN, Global Asthma and Allergy European Network; HIV/AIDS, human immunodeficiency virus/acquired immune deficiency syndrome.

### Data collection and study schedule

The cohort will be collected and registered using the routine clinical practice data of adult patients with CU. Data will be embedded based on multiple datasets, including (i) electronic health records, outpatient and inpatient claims data, and routine laboratory results; (ii) the Support System Pharmacy Dispensing extract, an administrative data source on pharmacy dispensing that provides patient-level details on medication utilization, dispensing detail, and health care costs; and (iii) Urticaria Care Database via REDCap^TM^, which provides patient-level details on sociodemographic and clinical characteristics, long-term urticaria care and monitoring, and PRO measures.

Participant recruitment will be performed continuously during the observation period to identify patients who are interested in participating in the CORE-CU registered cohort. Eligible participants will be monitored based on routine practice every 3 months (medical history, physical examination, and health care costs; further laboratory tests during study follow-up are needed in the case of clinically indicated) based on in-center follow-up care. Regarding PROs assessment, urticaria symptoms responses using participant self-reported diaries tools will be assessed monthly-basis. While HRQOL and mental health issue aspects will be evaluated and collected every 3 months during the CU clinic follow-up care. All the participants will be monitored for as long as possible; however, eligible participants will be assessed for at least one year (Table 3). If possible, after completing a one-year follow-up, participants will be reassessed and monitored based on the schedule of observation and procedures in the first year manner. Ultimately, participants will be followed and censored until the date of the earliest incidence of death, withdrawal for any reasons, transfer to another center, or loss to follow-up; whichever occurred first.

**Table 3 pone.0279566.t003:** Schedule of observation and procedures.

Parameter	Study Period: Time (Month)													
	Screening -1	Assessment and Follow-Up												
		0	1	2	3	4	5	6	7	8	9	10	11	12
Check eligibility against inclusion/exclusion criteria and medication review	X													
Gathering informed consent		X												
Sociodemographic and lifestyle data		X												
Medical history and physical examination		X			X			X			X			X
Patient-reported outcomes/experiences														
• Once daily/weekly UAS		X	X	X	X	X	X	X	X	X	X	X	X	X
• Short Form UCT		X	X	X	X	X	X	X	X	X	X	X	X	X
• PatGA-VAS		X	X	X	X	X	X	X	X	X	X	X	X	X
• PatGA-LS		X	X	X	X	X	X	X	X	X	X	X	X	X
• CU-Q_2_oL		X			X			X			X			X
• • DLQI		X			X			X			X			X
• EQ-5D-5L		X			X			X			X			X
• WHO-5 Well-being Index		X			X			X			X			X
• PHQ-9		X			X			X			X			X
• GAD-7		X			X			X			X			X
• SSS-8		X			X			X			X			X
• ISI		X			X			X			X			X
• WPAI: GH V2.1		X			X			X			X			X
• MAST		X			X			X			X			X
• Satisfaction with care		X			X			X			X			X
Routine laboratory tests (performed locally)		X												
Record medication changes		X			X			X			X			X
Health care costs: direct medical cost, direct non-medical cost, and indirect cost		X			X			X			X			X
Data monitoring		X			X			X			X			X
Statistical analysis and reporting														X

Abbreviations: CU-Q_2_oL, Chronic Urticaria Quality of Life Questionnaire; DLQI, Dermatology life Quality Index; GAD-7, Generalized Anxiety Disorder 7-item; ISI, Insomnia Severity Index; MAST, Medication Adherence Scale in Thais; PatGA-LS, Patients’s Global Assessment of Disease Control-Likert Scale; PatGA-VAS, Patient’s Global Assessment of Disease Severity-Visual Analogue Scale; PHQ-9, Patient Health Questionnaire 9-item; SSS-8, Somatic Symptom Scale 8-item; UAS, Urticaria Activity Score; UCT, Urticaria Control test; WPAI, Work Productivity and Activity Impairment Instrument.

To minimize participant dropout and missing data over time, the communications team and case manager staff members will facilitate cohort retention by employing various reminder approaches. Eligible participants will be contacted one day before the date of in-center visiting or the date of anticipated data collection based on participants’ preference contact methods (text message, phone, social media, or direct mail). During routine in-center follow-up care (every 3 months), participants will receive personalized health feedback and CU care management. Moreover, the study team will also share a lay language summary of study findings when available.

Participants will be asked to complete the urticaria symptoms and control diaries based on the international EAACI/GA^2^LEN/EuroGuiDerm/APAAACI guideline for the management of CU using daily urticaria activity score (daily UAS) and urticaria activity score over 7 days (UAS7). PRO measures, and health care utilization and costs were collected at baseline along with routine clinical urticaria monitoring visits.

Participant characteristics and routine laboratory data included the following:

Sociodemographic data (i.e., age, sex, marital status, education, income, health insurance, smoking and alcohol status, and body mass index)Medical history (i.e., history of drug/food/substance allergy, comorbid conditions, subtypes of CU) and physical examinationRoutine and urticaria-related laboratory tests (i.e., complete blood count, coagulogram, biochemistry, liver function test, thyroid function and anti-thyroid autoantibodies test, erythrocyte sedimentation rate, C-reactive protein, d-dimer, fibrinogen, total immunoglobulin E, antinuclear antibody test, serum levels of complement components [C3 and C4] and its activity [CH50], hepatitis B surface antigen, anti-hepatitis C virus antibody, stool parasite test, and *Helicobacter pylori* infection [if indicated])Medication utilization and adherence

### Pre-specified outcomes of interest

The pre-specified outcomes of interest and assessment of the CORE-CU cohort included the following (Table 3):

Clinical outcomes
Urticaria symptoms and severity using the daily urticaria activity score (daily UAS) and urticaria activity score over 7 days (UAS7) [1]Urticaria symptom control using the Short Form Urticaria Control Test (UCT) [14], Patient’s Global Assessment of Disease Control-Likert Scale (PatGA-LS) [15], and Patient’s Global Assessment of Disease Severity-Visual Analog Scale (PatGA-VAS) [15]Safety profiles: occurrence of adverse eventsPRO measures
HRQOL using the Chronic Urticaria Quality of Life Questionnaire (CU-Q2oL) [16], Dermatology Life Quality Index (DLQI) [17], and EuroQoL-5 dimension-5 level (EQ-5D-5L)Mental health issues and psychosocial problems using the Patient Health Questionnaire 9-item (PHQ-9) [18], Generalized Anxiety Disorder 7-item (GAD-7) [19], and the 5-item World Health Organization Well-being Index (WHO-5) [20]Symptom burden and impact on sleep using the Somatic Symptom Scale 8-item (SSS-8) [21] and Insomnia Severity Index (ISI) [22]Medication adherence using the Medication Adherence Scale in Thais (MAST) [23]Satisfaction with care using the global visual analog scale-10 cm and our team development version toolWork impairment using the Work Productivity and Activity Impairment Instrument (WPAI) [24]Health care utilization and economic outcomes
Health care costs: direct medical costs, direct non-medical costs, and indirect costsHospitalization, emergency visits, and extra/unplanned visits during the follow-up

### Statistical analysis plan

#### Sample size estimation

The sample size of participants was estimated based on the prevalence of adverse outcomes among CU patients, including (i) inadequate response to a standard dose of H1-antihistamines or uncontrolled urticaria symptoms (UCT score <12) with a range of 28.7%–82.8% [3, 8, 12, 13]; (ii) HRQOL impairment (DLQI >10 points) with a range of 30.9%– 31.5% [7, 8]; and (iii) mental health and psychosocial problems (depression, anxiety, insomnia, and somatic symptoms) with a range of 17.2%–55.7% [6, 7, 9]. With respect to a design effect of 2.0 and missing data of 20%, a target of at least 132 CU patients will be required for this study to ensure a 10% of margin of error and 0.05 type I error. Nevertheless, there will be no restrictions on the number of participants in this prospective longitudinal study.

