For cross-sectional analyses, the crude association among participant characteristics will be explored using the univariable logistic regression models to identify the candidate risk factors for adverse health outcomes. Subsequently, candidate risk factors with a *P*-value of <0.100 will be included in the multivariable logistic regression analysis with the backward elimination method. The variance inflation factors of risk factors within the multivariable model will be investigated to detect the multicollinearity of the final model. The odds ratios (ORs) with 95% CIs will be reported as the effect estimates of the final set of risk factor models for adverse health outcomes. For longitudinal analyses, changes in the adverse health outcome status during the follow-up period will be analyzed using multilevel logistic regression models with random intercepts to explore the associations with individual-level and baseline predictors.

All analyses will be performed using Stata software (version 16.0; StataCorp LP). Statistical significance for all tests will be two-tailed, with a *P*-value of <0.05. For participants with missing covariates, multiple imputation methods will be used to analyze incomplete datasets. However, variables containing more than 20% of missing data will be excluded from all analyses.

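### Enrolling 132 patients does not quite deliver the stated 10% margin of error once 20% of data are missing; the figure suggests that the 20% was added rather than divided out

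*Protocol article*

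**What the plan says.** The Sample size estimation section of the Protocol article bases the target on the prevalence of three kinds of adverse outcome:

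- Inadequate response or "uncontrolled urticaria symptoms (UCT score <12) with a range of 28.7%–82.8" per cent.
- "HRQOL impairment (DLQI >10 points) with a range of" 30.9% to 31.5%.
- Mental health and psychosocial problems ("depression, anxiety, insomnia, and somatic symptoms) with a range of 17.2%–55.7" per cent).

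The adjustments are given as "With respect to a design effect of 2.0 and missing data of 20" per cent. At least 132 patients are then said to be required "to ensure a 10% of margin of error and 0.05 type I error". The section adds that recruitment is not capped.

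The Statistical analysis section reports point prevalences with 95% confidence intervals and states: "Statistical significance for all tests will be two-tailed, with a" P-value threshold of 0.05. The article does not say which prevalence was used for planning, which formula was applied, what number of evaluable patients was required, or how the 20% entered the calculation.

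**The concern.** If a fraction m of enrolled patients will lack usable data, the required evaluable number must be divided by 1 − m. Multiplying by 1 + m gives too few. The stated 132 fits the multiplication and not the division. The text says that this number ensures the margin, so it should do so at least at the prevalence most favourable to the plan.

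What is at stake is the precision of descriptive prevalence estimates and whether the printed inputs and the printed target agree. The same step would also carry into any recalculation at another prevalence, where the gap in patients is larger.

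**Working it through.** **Inputs.** From Sample size estimation: margin d = 0.10 (read as the absolute half-width), alpha 0.05, design effect 2.0, missing data 20%, and the listed prevalences. From Statistical analysis: two-sided inference and 95% intervals, so z = 1.96. The planning prevalence p is not printed and has to be inferred.

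**Reproducing 132.** The usual precision formula is n0 = z² p(1 − p)/d².

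- At p = 0.172 (or 0.828): 1.96² × 0.172 × 0.828/0.01 = 54.71, rounded up to 55.
- Design effect: 55 × 2.0 = 110.
- Adding 20%: 110 × 1.2 = 132, an exact match.
- Dividing out 20%: 110/0.8 = 137.5, so 138. Rounding only at the end gives 109.42/0.8 = 136.8, so 137.

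**Other routes to 132.**

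- The same formula at the other listed range ends and at 50% gives about 189 to 233 with × 1.2, and about 197 to 243 with /0.8. None is near 132.
- A Wilson half-width at 17.2% needs 54, hence 108 after the design effect and 108/0.8 = 135. This is close but not a match, and 132 would still be short of it.
- A one-sided z of 1.645 at 28.7% gives 55.36 × 2.0 × 1.2 = 132.87, or 134 to 135 with rounding up at each step. It conflicts with the two-sided 95% intervals and also uses × 1.2.

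**What 132 delivers.**

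- Evaluable at 20% missing: 132 × 0.8 = 105.6, against 110.
- Missing data that 132 can absorb: (132 − 110)/132 = 22/132 = 16.7%.

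Half-width = 1.96 × √(2.0 × p(1 − p)/n):

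| p | n evaluable | Half-width (points) |
|---|---|---|
| 17.2% or 82.8% | 110 | 9.97 |
| 17.2% or 82.8% | 105.6 | 10.18 |
| 28.7% | 105.6 | 12.2 |
| 31.5% | 105.6 | 12.5 |
| 50% | 105.6 | 13.5 |
| 55.7% | 105.6 | 13.4 |

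The missing-data step accounts for about 0.2 points. The rest of the excess at the other prevalences comes from the choice of planning prevalence.

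**The case against.** - **The steps are not printed.** This stands. The prevalence, the 110 and the × 1.2 are reconstructions, and the full protocol may show something else. A reader might infer that the article itself documents a × 1.2 error. It does not; the exact match makes this the likeliest route and no more. The shortfall does not depend on that route, however. With the usual formula and 20% of enrolled patients missing, 132 misses 10 points at every listed prevalence.
- **The 20% may have been meant as an addition to the required number.** The article does not say what it is 20% of. Under that loose usage 132 is arithmetically right, but the wording describes a level of missing data, and at that level the margin is not met.
- **The effect is negligible.** Largely true: 10.18 rounds to 10, and these are descriptive estimates. A reader might infer that the study is underpowered or its conclusions unsafe. The sample size section makes no power claim, and 0.2 points would not undermine the estimates.
- **Recruitment is open.** Cohort status reports 75 patients enrolled and enrolment continuing, so a few more can be added within the plan. That makes the fix cheap, but 132 remains the stated minimum.
- **Multiple imputation may recover the loss.** Statistical analysis describes it for missing covariates, not expressly for the prevalence outcomes.
- **The design effect of 2.0 contains slack.** The study is single-centre with consecutive recruitment, and no cluster sampling is described. Without the factor, 105.6 evaluable patients give 7.2 points at 17.2% and 9.5 points at 50%. This softens the practical concern. The factor is nevertheless the plan's own input, so the printed figures still disagree.

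**Conclusion.** The point holds as a minor inconsistency between printed figures. At the most favourable listed prevalence, 132 enrolled with 20% missing leaves about 105 evaluable against 110. The margin is about 10.2 points where 10 is said to be ensured, a shortfall of 5 to 6 patients (about 4%).

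This rests on the usual single-proportion formula with z = 1.96, an absolute 10-point half-width, the stated design effect, and 20% read as a share of those enrolled. That the allowance was applied as × 1.2 is a strong inference, not a documented fact.

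A reader might also conclude that raising the target to 138 would secure a 10% margin for all the outcomes. It would not: 137 to 138 suffices only at 17.2% or 82.8%. The other listed prevalences, and 50%, need about 197 to 243 under the same inputs.

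**What to change.** In Sample size estimation, state the planning prevalence, show the steps, and apply n/(1 − missing). Then choose one of the following:

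- Set the minimum at 138 (137 if rounding only at the end), and say that the 10-point margin applies at 17.2%/82.8%.
- Keep 132, and say that at 17.2%/82.8% only it covers 16.7% missing data, or gives a 10.2-point margin at 20% missing.

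In either case, say that margins are wider at the other listed prevalences; with 132 enrolled and 20% missing they reach about 13.5 points at 50%.

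The cost is a few sentences and at most 6 more patients in an uncapped cohort, or no more patients if the figure is only restated.

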#### Statistical analysis

Preplanned statistical analysis will be performed based on one-year follow-up care (Table 3). The characteristics of the study cohort will be described as frequencies with percentages for categorical variables and mean ± standard deviation or medians with interquartile range for continuous variables as suitable. The differences between treatment groups (treatment-based non-sedating second-generation H1-antihistamines, biologics, or immunosuppressive agents) or severity strata of urticaria symptoms based on UAS7 (mild, 7–15 points; moderate, 16–27 points; and severe, 28–42 points) for categorical and continuous variables will be compared using Fisher’s exact test and analysis of covariance or Kruskal-Wallis test, respectively.

The point prevalence of adverse health outcomes (e.g., treatment responses [response vs. refractory to first-line therapy with non-sedating second-generation H1-antihistamines], symptoms controlled [uncontrolled, UCT <12 points vs. controlled, UCT ≥12 points], and occurrence of adverse mental health issues [including HRQOL impairment, depression, anxiety, insomnia, and somatic symptoms) will be estimated and reported corresponding to 95% confidence intervals (95% CIs). Subgroup analyses will be performed based on key patient characteristics (i.e., age of study participants, female sex, duration of CU, severity of urticaria symptoms, subtypes of CU, body weight/body mass index, total immunoglobulin E level, history of allergy or other systemic diseases, specific pharmacological treatments, and concomitant and rescue medications). In addition, one-year follow-up findings will be compared to assess the long-term response to the prevalence of adverse health outcomes. The overall trend analysis will explore the effect of over time across the cohort time frame.

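### With the plan's own design effect and missing-data allowance, 132 patients give a ±10-point margin only at the quoted prevalences of 17.2% and 82.8%; at the other quoted figures the margin is about ±12 to ±13 points

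*Protocol article*

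**What the plan says.** The Sample size estimation section of the Protocol article bases the target on three families of adverse outcome, each with a prevalence range from earlier studies:

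- (i) poor response to standard antihistamine treatment, or uncontrolled symptoms: 28.7% to 82.8%;
- (ii) "HRQOL impairment (DLQI >10 points"): 30.9% to 31.5%;
- (iii) mental health and psychosocial problems: 17.2% to 55.7%.

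The allowances are introduced by "With respect to a design effect of 2.0 and missing data of 20" (per cent). The result is "a target of at least 132 CU patients will be required for this study to ensure a 10% of margin of error", with a type I error of 0.05. The section then adds that enrolment is not capped. It names no single prevalence and does not tie the margin to one outcome.

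Two other sections bear on the calculation. Statistical analysis says that the point prevalences "will be estimated and reported corresponding to 95% confidence intervals (95% CIs"), and that "Statistical significance for all tests will be two-tailed". Study population says "Adult patients in an outpatient urticaria clinic will be consecutively recruited for this research".

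**The concern.** A precision-based sample size for a proportion depends on the assumed prevalence. The variance p(1 − p) is largest at 50% and falls towards either end. The quoted ranges together run from 17.2% to 82.8%, and two of them contain 50%. One figure of 132 with one margin of 10 points can cover all three families only if it was worked out at or near the worst case, and it was not.

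Prevalence with a 95% interval is a main planned estimate, and this paragraph is the only justification of the target. A reader would expect ±10 points for each outcome, when the stated assumptions give wider intervals for all of family (ii) and for nearly all of families (i) and (iii).

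**Working it through.** **Inputs**, all from the Protocol article. Margin d = 0.10 and α = 0.05 ("to ensure a 10% of margin of error and 0.05 type I error"). Two-sided z = 1.96, from the two-tailed tests and 95% intervals in Statistical analysis. Design effect 2.0, missing data 20%, and the prevalence ranges given above. The value 50% is not quoted as such, but lies inside ranges (i) and (iii).

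**Step 1: reproduce 132.** For a single proportion, n0 = z² p(1 − p) / d². At p = 0.172 (p = 0.828 gives the same product):

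n0 = 1.96² × 0.172 × 0.828 / 0.10² = 54.7, rounded up to 55; 55 × 2.0 = 110; 110 × 1.2 = 132.

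This matches exactly. No other quoted prevalence gives 132 with the two-sided formula. A one-sided z of 1.645 at 28.7% with ×1.2 gives 133, but that conflicts with the two-tailed tests and 95% intervals.

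**Step 2: number needed for ±10 points, and margin delivered by 132.** Needed: n0 × 2.0 × 1.2, or n0 × 2.0 / 0.8. Delivered: 1.96 × √(p(1 − p)/n_eff), with n_eff = 132/1.2/2.0 = 55 under the ×1.2 convention, or 132 × 0.8/2.0 = 52.8 if 20% are actually lost.

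| Prevalence | n0 | Needed, ×1.2 | Needed, /0.8 | Margin, n_eff 55 | Margin, n_eff 52.8 |
|---|---|---|---|---|---|
| 17.2% or 82.8% | 54.7 | 131.3 | 136.8 | ±9.97 | ±10.18 |
| 28.7% | 78.6 | 188.7 | 196.5 | ±11.96 | ±12.20 |
| 30.9% | 82.0 | 196.9 | 205.1 | ±12.21 | ±12.46 |
| 31.5% | 82.9 | 198.9 | 207.2 | ±12.28 | ±12.53 |
| 50% | 96.0 | 230.5 | 240.1 | ±13.21 | ±13.49 |
| 55.7% | 94.8 | 227.5 | 237.0 | ±13.13 | ±13.40 |

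**Step 3: where ±10 is reached.** With n_eff = 55, the margin is 10 points or less only for prevalences up to 17.3% or from 82.7% upwards. With n_eff = 52.8 the limits are about 16.5% and 83.5%, which lie outside all three quoted ranges. Prevalences between 17.2% and 28.7%, or between about 71% and 82.8%, give roughly 10 to 12 points.

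**Step 4: missing-data factor.** If 20% of 132 are missing, 132 × 0.8 = 105.6 remain, whereas 132/1.2 = 110 were wanted. Multiplying by 1.2 does not fully offset a 20% loss; dividing by 0.8 does. At 17.2% this moves the requirement from 132 to 137 and the margin from ±9.97 to ±10.18. It is a minor point.

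**Step 5: without the design effect.** With 105.6 evaluable patients at p = 0.50: 1.96 × √(0.25/105.6) = ±9.54 points, the widest at any prevalence.

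**Step 6: choice of interval.** Wilson half-widths show the same pattern: about 9.9 to 10.1 points at 17.2%, and 11.6 to 13.0 at the other values in the table.

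**The case against.** The strongest reply is that 132 is a floor in an uncapped observational registry, so precision can only improve with further enrolment. That is true, but the sentence attaches the margin to 132 itself ("to ensure a 10% of margin of error"), and 132 is the only minimum given.

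A second reply is that the shortfall exists only because of the design effect: without it, 132 meets ±10 points at every prevalence. This stands, and it limits the consequence. The target may well be adequate; its stated justification is not, because the plan says that it applies the factor of 2.0.

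A third reply is that the article does not print its formula, so the use of 17.2% or 82.8% is inferred. That also stands, although no other quoted prevalence gives 132 with the two-sided formula.

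The documents do not support several stronger readings that a reader might draw:

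- That every outcome other than one misses by 12 points or more. The values 17.2% and 82.8% are endpoints of families (iii) and (i), and values near them give 10 to 12 points. Only family (ii) lies wholly above 12.
- That the design effect is baseless. One clinic and individually recruited patients give no obvious reason for 2.0 in a single-visit prevalence. But patients are measured repeatedly and longitudinal multilevel models are planned, and the rationale may stand in the full protocol, which is not shown.
- That the planned confidence intervals will ignore the design effect. The article gives no interval method.
- That the most favourable prevalence was picked on purpose. Nothing in the text shows how the value was chosen.

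**Conclusion.** The point holds. Under the plan's own inputs, 132 gives a 10-point margin only at the two extreme quoted prevalences, and there only with the ×1.2 inflation. At the other quoted figures the margin is ±12.0 to ±13.1 points (×1.2), or ±12.2 to ±13.4 (20% actually lost). At 50% it is ±13.2 to ±13.5. Family (ii) misses over its entire range, at ±12.2 to ±12.5.

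This rests on a two-sided 95% interval for a single proportion, a margin read as absolute percentage points, and the design effect being applied as stated. It is an error in the precision claimed, not proof that the cohort is too small.

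**What to change.** Rewrite the sample size paragraph so that it:

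1. names the prevalence from which 132 was derived;
2. allows for missing data by dividing by 0.8, which is the same as counting 132 × 0.8 evaluable patients;
3. replaces the blanket ±10% with the precision that 132 delivers under the stated inputs: about ±10.2 points at 17.2% or 82.8%, ±12.5 for quality-of-life impairment, and up to ±13.5 at 50%.

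Alternatively, if the investigators confirm that the design effect does not apply to a single-visit prevalence in individually recruited patients at one clinic, they can remove it and state that 132 with 20% missing gives about ±9.5 points or better at any prevalence. That is for them to confirm, since their reason for 2.0 is not shown.

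Neither route adds patients. A target of 241 (240.1 rounded up) would be needed only if the design effect is kept and ±10 points is still promised at 50%. The cost is one rewritten paragraph and, if the design effect is kept, a less favourable stated precision.
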